## Program Attendance/Adherence

The participants will be asked to attend the PEP-Aut sessions twice a week, during the regular attending hours at the SEC-Aut, for a period of 48 weeks. The intervention with PE will last for a total of 40 weeks, including a total frequency of 80 exercise sessions and 4 weeks of preevaluation and 4 weeks of postevaluation. Attendance will be recorded, and in the case of two consecutive absences, we will use the following procedures: (a) telephone contact, made by institutional social services, to parents or legal guardian to identify reasons related with the absences; and (b) home visit to identify reasons related with the absences. There was no guidance from previous studies on the expected percentage of adherence to PE intervention programs in children, adolescents, and adults with ASD (44), so a cutoff value for inclusion of participants in final statistics will be determined following the attendance rates seen in the pilot study.

## Masking

Blood samples collection and global health assessment will be performed by a registered nurse and a certified medical doctor. The anthropometric and physical fitness assessment will be performed by a certified member of the research team with expertise in both exercise and services provided to children and youngsters with ASD. The administration of the questionnaires to parents and legal representatives, assessing the socioeconomic status, the health-related quality of life, and the administration of the Scale of Autistic Traits (SAT) and the Childhood Autism Rating Scale (CARS) will be organized by the main investigator and will be performed together with a certified psychologist working with the research team. To minimize differences in the procedures, the same evaluators will perform data collection in the different assessment moments over the study. Each member of the assessment team will collect the same specific data, will not make any reference to the exercise program, and will not have any access to the remaining data.

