## Outcome Measures

All outcome measures will be collected two times: (a) in Phase 1 (cross-sectional study, weeks 1–12) and (b) in Phase 2 (intervention study, between weeks 13–16 and 57–60). Primary outcomes are related to the symptoms profile and the level of PA. Secondary outcomes will be the metabolic profile, the anthropometric measurements, the functional level, the handgrip strength, the socioeconomic status, and the health-related quality of life. A characteristic of this study is that some of the measurements are applied to participants families or legal representatives (Socio-economic Questionnaire, Child Health Questionnaire, SAT, and CATS), while others are applied to the participants with ASD themselves (PA level, anthropometric measures, aerobic function, hand-grip strength, and blood collection).

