### Blood Sample and Analysis

Blood will be collected by venepuncture, in a fasting state, by an independent registered nurse and will be analyzed using a standard protocol (83) by a previously defined certified laboratory. Individual results are sent to the research leader in a printed format and without any storage of the biological material collected. Children’s parents or legal representatives will receive a copy of the individual lab test results containing individual information about the child’s metabolic profile (glucose, total cholesterol, triglycerides, HDL, and LDL).

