### Adaptation (4 Weeks)

The purpose of this phase is to enable children with ASD to adjust their behavior to the characteristics of the different exercises and tasks included in PEP-Aut (see Table 1). Adaptive sessions will be mediated by parents or legal representatives and supervised by the researcher.

**Table 1 T1:** Overview of the PEP-Aut specific physical exercises used for intervention.

Exercise	Physical ability	Description	Resource
Climbing and support in the bar	Upper limb strength	The child should climb a vertical backrest, reach the last bar, and hold the body suspended for 5.0 s	One standard vertical backrest with 1.5 m height, fixed at 0.5 m of the ground
Release to the basketball	Upper limb strength	Starting from an initial position with a mini medicinal ball close to the chest, the child should perform a shoulder lift (180°) followed by an elbow flexion, positioning the mini ball over the head. From this position, the child should then do a full extension of the upper limbs (elbow and forearm) followed by a slight flexion of the wrist, performing the ball throwing movement	One basketball table (fixed at 1.75 m from the floor), three benches to support the throwing with different dimensions (base 0.5 cm × height 0.5, 1.0, and 1.5 m); Mini medicinal balls with different weights (0.5, 1.0, and 2.0 kg)
Elastic bands workout	Upper and lower limbs strength	The child in an upright position, with the arms suspended along the body, picks up the elastic bands, which should be fixed to the floor by a safety beam, by the fists. The child should perform a simultaneous flexion of the forearms, bringing the hands closer to the shoulders for each repetition	Elastic bands
Climbing the steps and walking on the inclined plane	Lower limbs strength and coordination	The child should climb the three steps and walk on the inclined plane (hip and knee flexion movement)	l-shaped wooden staircase with three steps (0.12 m × 0.15 m) and inclined plane of 0.78 m length and 0.30 m height with handrail throughout the entire length

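### The Masking section states no masking to allocation for SAT, CARS and CHQ, and the parents who supply the answers know the arm

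*Protocol article*

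**What the plan says.** The protocol article has a section headed Masking. For SAT, CARS and the questionnaires given to parents, it says that administration "will be organized by the main investigator and will be performed together with a certified psychologist working with the research team". It then lists three safeguards. To reduce procedural differences, "the same evaluators will perform data collection in the different assessment moments over the study". Each member of the assessment team "will not make any reference to the exercise program, and will not have any access to the remaining data".

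Under Outcome Measures, "Primary outcomes are related to the symptoms profile and the level of PA". The same section says that "some of the measurements are applied to participants families or legal representatives (Socio-economic Questionnaire, Child Health Questionnaire, SAT, and CATS"; the last abbreviation is taken here as a misprint for CARS.

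The comparison is exercise against usual daily activities with no exercise programme (Methods/Design). On the parents' part in the programme, the article says: "Adaptive sessions will be mediated by parents or legal representatives and supervised by the researcher" (Adaptation). The section on equipment with minor body contact also defines the mediator as a parent or legal representative. In the 40-week programme, parents are present at sessions (Implementation of the PEP-Aut Session's Duration) and carry out the relaxation exercises that close each session (Intervention).

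**The concern.** A section with this heading should tell the reader who does not know the allocation. This one describes who collects what, and limits on conversation and data sharing, but names nobody who is kept unaware of the arm.

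The gap matters most for the symptom scales. They depend on judgement, their informants know the arm, and on the natural reading the main investigator takes part in administering them. The Discussion states the study's premise that exercise reduces stereotypic behaviour, so an expectation of benefit is on record. SAT and CARS are also the only symptom instruments the article describes, so there is no masked symptom measure to fall back on. If families or raters lean towards the expected result, part of any between-arm difference on a primary outcome would be reporting and not response to exercise. Neither a larger sample nor the multilevel model would remove that.

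**Working it through.** The article gives no figure for this point, so the first part of the check sets its statements side by side.

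**1. Do the stated safeguards hide the arm?**

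| Safeguard (Masking) | What it does | Hides allocation from the rater? |
|---|---|---|
| No reference to the exercise programme | Limits what the assessor says to families | No |
| No access to the remaining data | Limits influence from other measurements | No |
| Same evaluators at each assessment | Consistency over time | No |

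**2. Do the informants know the arm?** SAT, CARS and CHQ are applied to families (Outcome Measures). Control families see that their child has no programme (Methods/Design). Exercise-arm families mediate the adaptation sessions (Adaptation; With Minor Body Contact), are present at sessions (Implementation of the PEP-Aut Session's Duration) and deliver the relaxation phase (Intervention). Informants in both arms therefore know the allocation.

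**3. Is a primary outcome affected?** Yes. The symptoms profile is primary. The other primary outcome, physical activity level, is recorded by accelerometer (Assessment of Children's PA) and does not pass through an informant's rating.

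**4. What could a reporting shift do?** The article gives no size for it, so this is an illustration under assumed values and not an estimate.

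- Inputs from Estimated Sample Size: total N = 39 (needed) and N = 51 (selected).
- Assumptions: equal arms, a two-sided t-test at 0.05, a true effect of zero, and a shift b (in SD units) favouring exercise that comes from unmasked reporting alone.
- Formula: with m = N/2 per arm, the test statistic follows a noncentral t distribution with N − 2 degrees of freedom and noncentrality b × √(m/2).
- N = 39: √(19.5/2) = 3.12. N = 51: √(25.5/2) = 3.57.

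| Assumed shift b | N = 39: noncentrality | P(significant) | N = 51: noncentrality | P(significant) |
|---|---|---|---|---|
| 0 | 0 | 5.0% | 0 | 5.0% |
| 0.2 SD | 0.62 | 9.3% | 0.71 | 10.8% |
| 0.3 SD | 0.94 | 15.0% | 1.07 | 18.3% |
| 0.5 SD | 1.56 | 33.1% | 1.79 | 41.7% |

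Nearly all of the excess favours exercise: at 0.2 SD that tail alone is 8.8% (N = 39) and 10.4% (N = 51), against a nominal 2.5%. The problem grows with sample size, as bias does. The planned multilevel analysis would have a different standard error, so the exact percentages would change but not the direction.

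**The case against.** The strongest reply is that parents cannot be masked in a comparison of exercise with usual activities, and that the Masking section never claims they are. Both statements are true. What the text lacks is a disclosure and a masked rater where one is possible; it does not contain a false claim of blinding.

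A second reply is that the main investigator may only organise the assessments while the psychologist performs them. Joint administration is the natural reading, but the wording leaves room for the other, and who scores is not stated. Even so, nothing says that the psychologist is unaware of the arm.

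A reader might infer more than the article supports:

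- *That the main investigator also supervises sessions and is known to hold the allocation.* The article refers separately to a main investigator, a researcher who supervises the adaptation sessions, and a research leader who receives laboratory results. It never says they are one person, and it does not say who holds the allocation.
- *That laboratory reports, or the use of SAT items to choose the level of mediation, unmask the rater.* Neither passes the allocation to the person rating symptoms.
- *That parents act as mediators for all 40 weeks.* Parental mediation is explicit for the adaptation sessions. For the 40 weeks, the text supports presence and the relaxation phase, in the exercise arm only.
- *That SAT or CARS is the single primary outcome.* Estimated Sample Size names the occurrence of stereotyped behaviours and ties it to no instrument. Outcome Measures gives the broader symptoms profile, which SAT and CARS most plausibly measure.
- *That accelerometry can check the parent reports.* Physical activity is a different construct and can change without symptoms changing, or the reverse.

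**Conclusion.** The point holds in this form. The section headed Masking states no masking to allocation for the people who take SAT, CARS and CHQ, and its safeguards do not provide any. The parent informants know the arm. A symptom difference, on a primary outcome, may therefore partly reflect expectation.

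The size is unknown. Under assumed shifts of 0.2 to 0.5 SD, the chance of a significant result with no true effect would be about 9% to 33% with 39 children and about 11% to 42% with 51. These figures rest wholly on the assumed shift and on a simple two-arm t-test.

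The conclusion assumes that the printed CATS means CARS and that the symptoms profile is measured by SAT and CARS. It does not depend on the main investigator having any role in the sessions. The accelerometer outcome is not affected by rating bias of this kind. The trial remains usable, but its symptom result needs a better-protected rating and a plainer statement of its limits.

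**What to change.** At both Phase 2 assessments (weeks 13–16 and 57–60):

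1. Have the psychologist already on the team administer and score SAT, CARS and CHQ without the main investigator. The psychologist should have no session role and no access to the allocation.
2. Rate CARS the same way at both time points and include observation of the child, so that at least one symptom rating does not rest on parent report alone. The article already describes CARS as evaluating the child's behaviour. Changing the rater or the mode only at follow-up would break comparability with baseline and the same-evaluator rule.
3. Ask families not to disclose the arm to the psychologist.
4. State in the Masking section who is masked and who is not, that SAT and CHQ are unblinded parent reports, and that conclusions from them are limited accordingly.

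The cost is a reassignment within the existing team and a few sentences of text. There are three drawbacks. Investigator oversight of the interviews is reduced. The procedure may differ from Phase 1; because the Abstract calls Phase 1 the baseline of the next phase, the weeks 13–16 values should serve as the baseline for these scales. Parent reports also remain unblinded, and families may still reveal the arm, so the bias is reduced and not removed.

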## Outcome Measures

All outcome measures will be collected two times: (a) in Phase 1 (cross-sectional study, weeks 1–12) and (b) in Phase 2 (intervention study, between weeks 13–16 and 57–60). Primary outcomes are related to the symptoms profile and the level of PA. Secondary outcomes will be the metabolic profile, the anthropometric measurements, the functional level, the handgrip strength, the socioeconomic status, and the health-related quality of life. A characteristic of this study is that some of the measurements are applied to participants families or legal representatives (Socio-economic Questionnaire, Child Health Questionnaire, SAT, and CATS), while others are applied to the participants with ASD themselves (PA level, anthropometric measures, aerobic function, hand-grip strength, and blood collection).

## Assessment of Parents and Legal Representatives

### Socioeconomic Status

A questionnaire developed by the Brazilian Association of Market Research Institutes, version 2012, which is based on the family budget survey of the Brazilian Institute of Geography and Statistics (IBGE), will be used to estimate the purchasing power of individuals and families and to define economic classes. The questionnaire considers consumption patterns or potentials (television, radio, bathroom, automobile, house cleaner, washing machine, video cassette and or DVD, refrigerator, and freezer), and level of schooling of the head of the family (from illiteracy to higher education level complete). Each item is classified using a Likert-type scale (0–4) with specific punctuation for type and number of items. The sum of the items (0–46 points) allows the definition of the economic class (A1, A2, B1, B2, C1, C2, D, and E), where A1 represents the highest economic status, monthly income of R$12,926, and E represents the lowest economic status attributing monthly income of R$477, lower than the Brazilian minimum wage (66).

### Child Health Status

We will use the Child Health Questionnaire (CHQ-PF50), which is a generic instrument to assess the quality of life related to physical and psychosocial health in childhood from the parents’ perception (67). The instrument has 50 items organized in 15 domains: physical capacity, social role of limiting daily activities due to emotional and behavioral aspects, social role of limiting daily activities due to physical capacity, body pain or discomfort, behavior, mental health, self-esteem, health status, family impact, and family cohesion (68). The score of each domain is presented on a scale of 0–100, with the highest score representing the best state of health, well-being, and satisfaction. Additional information on this instrument is available at https://www.healthactchq.com/.

We will use the Brazilian Portuguese version of the CHQ-PF50 (68). The questionnaire was translated and validated in the context of the Brazilian population with chronic disease. The validation study reported Cronbach’s alpha values above 0.70 in 10 (91%) of the 11 measurable health concepts (i.e., health concepts with more than one item) of CHQ (total 0.94, range, 0.40–0.94), except for the perception of health status (0.40). Reliability based on the repeated measurements within an average of 8.5 days showed intraclass correlation coefficients with an overall mean of 0.60 (0.20–0.90) for the 15 health concepts evaluated by the CHQ, thus acceptable reproducibility. The concepts with the lowest reproducibility were those related to the social role of limiting daily activities due to physical capacity, perception of health status, change in health status, and emotional impact in the family.

### Childhood Autism Rating Scale

Childhood Autism Rating Scale is a standardized instrument to identify levels of intensity of ASDs (mild, moderate, and severe), as well as the sharp distinction between autism and intellectual disability (69). The instrument is based on the diagnostic criteria of Kanner (70), Creak (71), Rutter (72), Ritvo and Freeman (73), and DSM, third edition (DSM-III). The Brazilian Portuguese version of this instrument (CARS-BR) (69) will be used to evaluate the child’s behavior from 14 domains that are usually affected by serious problems in autism, plus a general category of autism impressions. The aim of the instrument is to identify children with ASD and differentiate them from children with other developmental disorders. The 15 items of the scale are relative to people, imitative behavior, emotional response, body use, use of object, adaptation to change, visual response, auditory response, perceptual response, fear or anxiety, verbal communication, non-verbal communication, activity level, level and consistency of intellectual relations, and general impressions. The score ranges from 1 to 4 for each item: 1 indicates adequate behavior for the age level, while 4 indicates severe deviation from normal behavior for the age level. The scores of the individual items are summed in a total score, which rates the child as non-autistic (below 30), mildly or moderately autistic (30–36.5), or severely autistic (above 36.5). It is also necessary to count the number of items in which the child scored at or above 3. A diagnosis of severe autism is appropriate if these items are at least 5. A score of 30 or more is used as the threshold value for diagnosis of autism.

The validation process was attended by 60 patients and, in terms of validity, demonstrated a very good internal consistency, with mean values of Cronbach’s alpha coefficient of 0.82 (95% CI, 0.71–0.88), indicating a high degree of internal consistency (69, 74). Data on the convergent validity, compared to the Autistic Traits Assessment Scale, showed Pearson’s correlation coefficient values with *r* = 0.89. The test–retest reliability had a kappa coefficient value of 0.90.

### Scale of Autistic Traits

The SAT is an instrument that allows a first identification of the symptoms profile of ASDs (75). In its original construction, the diagnostic criteria of DSM-III, DSM-III-R, and ICD-10 were considered to develop the instrument. The ATA scale is an easy-to-apply instrument, accessible to professionals who have direct contact with the autistic population (e.g., teachers or even parents) informing the current state of the patient. The instrument was developed to be used by professionals, not necessarily medical doctors, responsible for the evaluation of the answers according to each item. It is not, therefore, a diagnostic interview, but a standardized test that gives the cognitive behavioral profile of the child with ASD. The scale score is based on the following criteria: (i) each subscale of the test has a value from 0 to 2; (ii) the positive scale is scored when one of the items is positive; (iii) the overall scale score is based on the arithmetic sum of all the positive values of the subscale, allowing a very precise characterization of autism.

The Brazilian Portuguese translation and validation considered corrections of the diagnostic criteria, resulting from the publication of the DSM-IV (76). The cutoff point was 15 (*p* ≤ 0.05); the coefficient of variation (reliability) was 0.27, and the external validity showed low agreement (kappa = 0.04). Finally, the internal validity was 100%, showing that the clinical diagnoses agreed with the results obtained by applying the scale. The correlation value obtained was 0.42, being specific for the autistic conditions. It also presented good internal consistency, with Cronbach’s alpha 0.71. Thus, the scale is considered to be adequate and reliable for us to use in our applied educational context, with children and young people involved in PE.

### Assessment of Children’s PA

ActiGraph tri-axial accelerometers will be used to assess the children’s PA level. The accelerometer allows the recording of body acceleration in the lateral, vertical, and anteroposterior axes, and their respective magnitude vectors. We will program the accelerometers to record epochs at each second, and subsequently, in the data reduction phase, the epochs will be grouped into blocks of 15 s. A consecutive period of 90 min without any record of body acceleration is considered as non-use time of the apparatus and will be excluded in the data reduction phase (77). The cutoff points adopted for the determination of PA intensities are sedentary (equal to or less than 1,099 cpm); light (1,100–3,199 cpm); moderate (3,200–8,199 cpm); and vigorous (equal to or greater than 8,200 cpm) (78, 79).

### Anthropometric Measures

Anthropometric measures will take place separately, in a private room, following standardized procedures (80). Data collection will include a set of simple anthropometric variables such as total body mass (kilograms); stature (centimeters); BMI (kilogram per square meter); waist circumference (centimeters); and triceps, biceps, calf, subscapular, supra iliac, and abdominal skinfolds (millimeter). Body mass (kilograms) will be determined with a portable digital scale (Seca^®^, Model 770, Birmingham, UK). Stature (centimeters) will be determined with a portable stadiometer (Seca^®^, Model 206, Birmingham, UK) with a precision of 0.1 cm, waist circumference (centimeters) will be measured with an anthropometric tape (Seca^®^, Model 201, 205 cm) with a precision of 0.1 cm, and skinfolds will be measured with an adipometer (millimeter) (Model OPUS^®^ Max 30).

